# 2.0 Scientific abstract

**Background:** Anxiety disorders are among the most prevalent psychiatric disorders in the Canada Post workers general population, yet there is a lack of information with regards to safety and efficacy of combined naturopathic approache for anxiety. There is a body of literature that supports usage of some herbs, dietary advice, exercise, and cognitive techniques in the treatment of anxiety, however there is very little research on the combined approach in a workplace setting. We aim to evaluate the efficacy and safety of dietary advice, exercise, cognitive counselling, Withania sominfera and a Adult Multi One multivitamin on common indicators of anxiety

**Design:** Phase II Randomised parallel clinical trial.

**Objective:** To determine if dietary modification, exercise, counselling, Withania somnifera, and a multi vitamin decreases the anxiety scores in a working population at Canada Post.

**Null hypothesis:** Dietary modification, exercise, counselling, Withania somnifera, and a multi vitamin has no effect on anxiety scores.

**Participants:** 80 Canada Post employees who are who are experiencing the symptoms anxiety (who score over 10 points on the Beck Anxiety Inventory) will be randomised to two groups: one receiving dietary modification, exercise, counselling, Withania somnifera, and a multi vitamin (active group), and one receiving dietary modification, exercise, counselling, and placebo (control group).

**Setting:** Clinical trial will be conducted at the Canada Post Gateway Processing Plant.

**Intervention:** Baseline assessment of both groups will include blood pressure, orthostatic blood pressure, and completion of the Beck Anxiety Inventory (BAI), SF-36, and The Fatigue Questionnaire to determine severity of anxiety symptoms. The active group will receive instruction on stress reduction techniques including diaphragmatic breath control, encouragement to exercise, counselling to identify and eliminate negative stress coping patterns, dietary counselling to ensure proper nutritional content of foods, and reduce reactive hypoglycaemia, Withania somnifera, and a multi vitamin for 12 weeks. The control group will receive instruction on stress reduction techniques including diaphragmatic breath control, encouragement to exercise, counselling to identify and eliminate negative stress coping patterns, and placebo. Every 4 weeks (day 28, day 56) both groups will again have their sitting and orthostatic blood pressure checked, and complete the BAI, SF-36, and The Fatigue Questionnaire. On day 84, a final assessment of sitting and orthostatic blood pressure, BAI, SF-36, and The Fatigue Questionnaire completion will take place.

**Main Outcome Measures:** ***The Beck Anxiety Inventory (BAI)*** is designed to discriminate anxiety from depression in individuals. The BAI consists of 21 items, each describing a common symptom of anxiety. The items are summed to obtain a total score that can range from 0-63. The scale has high internal consistency. ***The short form –36*** (SF-36) questionnaire is a self-administered, 36-item questionnaire that measures health-related quality of life in eight domains: 1) physical functioning, by measuring the ability to perform a variety of daily activities and tasks that require physical effort (10 items); 2) role limitations due to physical problems(4 items); 3)role limitations due to emotional problems (3 items); 4) vitality, measuring perceived level of energy and fatigue (4 items); 5) freedom from bodily pain (2 items); 6)social functioning (2 items); 7) mental health, by measuring both negative and positive emotional states (5 items) and 8)general health perceptions (6 items). Both physical and mental summary scores can be obtained. Each domain is scored separately from 0 (lowest level) to 100 (highest level). Two summary scores can be calculated from information obtained in the 8 domains- Physical Function and Mental Health Summary Scores. ***The Fatigue Questionnaire*** is an 11-item instrument developed for use in population studies to measure physical and mental aspects of fatigue, a feature commonly observed in many somatizing patients. Each item has 4 response options, with high scores corresponding to high levels of fatigue.

**Relevance:** Many patients seek alternatives to conventional anxiety treatments. To date, no study has evaluated the potential for the combined efficacy of dietary, counselling, exercise, Withania somnifera and a Adult Multi One multivitamin to effectively treat anxiety. Knowledge of the efficacy, safety or risk of natural health products, especially one already on the market is important for physicians and the public in order to make informed decisions.

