On subsequent visits, both the control and intervention group patients will receive treatments including cognitive behavioural stress reduction, behavioral psychotherapy, examination of sleep patterns and treatment for any insomnia. Both groups will be encouraged to engage in an active exercise routine. The active group will also receive daily good quality multi vitamin (Ultra Balance III by Douglas Labs) and *Withania somnifera* (300 mg standardized to 1.5% Withanolides, bid) (Ashwagandha by Douglas Labs). The control group will receive placebo identical in look and frequency of dosage to the treatment group. On subsequent visits, the active group will receive lifestyle and diet counseling, and will continue with behavioral psychotherapy. Active group patients will also receive acupressure massage for at least 15 minutes once per week.

Both the active and control arm will attend weekly 30 minute treatments, for a total of 12 treatments over 12 weeks. Both groups will complete the Beck Anxiety Inventory, S-90-R, SF-36, Fatigue Questionnaire, and the Perceived Benefit of Treatment questionnaires at 4, 8, and 12 weeks. At these times, the sitting and orthostatic blood pressures will also be recorded. Both groups will also hand in the Pain Diet, Absenteeism, Pain Medication and Therapies Diary every week.

Study period is 12 weeks. Clinical evaluations will be performed at:

- Baseline (Visit 1 - Day 1)
- Interim for the treatment groups: (Visit 2 - Day 7, Visit 3- Day 14, Visit 4 – Day 21, Visit 4 – Day 28, Visit 5 – Day 35, Visit 6 – Day 42, Visit 7 – Day 49, Visit 8 – Day 56, Visit 9 – Day 63, Visit 10 – Day 70, Visit 11 – Day 77)
- Interim for the control groups: (Visit 2 - Day 7, Visit 3- Day 14, Visit 4 – Day 21, Visit 4 – Day 28, Visit 5 – Day 35, Visit 6 – Day 42, Visit 7 – Day 49, Visit 8 – Day 56, Visit 9 – Day 63, Visit 10 – Day 70, Visit 11 – Day 77)
- End of Treatment (Visit 12 - Day 84), Questionnaires and Medication diaries filled in for the last time

Follow-up data will be collected at 2, 6, and 12 months post treatment via a mailed questionnaire package containing the Beck Anxiety Inventory, S-90-R, SF-36, Fatigue Questionnaire, and the Perceived Benefit of Treatment questionnaires, as well as the Diet, Absenteeism, Medication and Therapies Diary. Non-responders will receive reminders by post. If this is unsuccessful, the patients will be telephoned.

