**Outcome measurements**

We will determine if naturopathic medical interventions (*Withania somnifera* extract, daily multi-vitamin, dietary modifications, cognitive-behavioral exercises, relaxation techniques and acupressure massage) reduces the incidence of specific symptoms as measured by the Beck Anxiety Inventory as shown in appendix A. This scale has been independently validated.

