# 4.0 Justification of Methodology

The study trial shall involve 78 subjects as determined above. The trial shall last 84 days (12 weeks) which is greater than the mean treatment time for most trials reviewed and we feel enough time to determine whether a clinically significant effect will be produced. Longer duration would not likely show much more increased effect but rather might jeopardise the results through loss of participation and or incorporation of other treatments. The extended duration will ensure all active substances are metabolised and will allow for more accurate data collection on the effects of naturopathic medical treatments.

We employed a controlled design, rather than the conventional before/after design employed by many intervention studies as we wish to assess not only activity in the treatment group but also to determine if any change is significantly different from a control group not receiving the intervention. The absence of a control group would make it impossible to determine if variability in metabolism within individuals has overshadowed the potential impact of naturopathic medical treatments on anxiety symptoms. Examples of factors that could influence variability within individuals include changes in stimulant use, sleeping habits, compliance to treatment interventions, exercise levels and environmental stressors that may occur over the course of the study. Traditional drug intervention studies that are not controlled are inherently susceptible to bias and it is very difficult to determine if the results have been skewed.

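### The objective and null hypothesis concern the whole package, but exercise and counselling go to both arms, so the randomised comparison tests only an add-on effect, and the add-on is not consistently defined

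*Protocol*

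**What the plan says.** The abstract (Protocol 2.0) sets the aim as "To determine if dietary modification, exercise, counselling, Withania somnifera, and a multi vitamin decreases the anxiety scores" and the null hypothesis as "Dietary modification, exercise, counselling, Withania somnifera, and a multi vitamin has no effect on anxiety scores". Neither names a comparator. Section 3.0 (Proposed Study) repeats the aim in substance. The Outcome measurements paragraph opens with "We will determine if naturopathic medical interventions" and goes on to a list that includes cognitive-behavioural exercises, relaxation and acupressure.

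The control arm is described as follows:

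- Abstract, Participants: "one receiving dietary modification, exercise, counselling, and placebo (control group".
- Abstract, Intervention: instruction in stress reduction, then "encouragement to exercise, counselling to identify and eliminate negative stress coping patterns, and placebo". Dietary counselling is listed for the active arm and not for control.
- Methodology: "both the control and intervention group patients will receive treatments including cognitive behavioural stress reduction, behavioral psychotherapy", and "Both groups will be encouraged to engage in an active exercise routine". Lifestyle and diet counselling, and weekly acupressure, are assigned to the active group.

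Section 4.0 (Justification of Methodology) says the controlled design was chosen to "determine if any change is significantly different from a control group not receiving the intervention".

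**The concern.** A hypothesis about a package needs a comparison with people who do not get the package. Here the control arm gets a substantial part of it. Two misreadings follow. If the arms differ, the result could be credited to exercise and counselling, on which the comparison is silent. If they do not differ, the stated null invites the conclusion that the package does nothing, although both arms may have improved on the shared programme.

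The second outcome is realistic on the Protocol's own account. The section of the Introduction on naturopathic treatments says that cognitive-behavioural methods lower anxiety and that therapies aimed at coping patterns are effective. The main efficacy conclusion is at stake, and so is the cost-effectiveness work for which the Relevance section says the trial will prepare the ground.

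**Working it through.** **1. What each description gives to each arm**

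| Component | Abstract, Participants | Abstract, Intervention | Methodology | 3.3 Timeline | In objective and null? |
|---|---|---|---|---|---|
| Exercise encouragement | both | both | both | not listed | yes |
| Counselling / cognitive-behavioural treatment | both | both | both | given to subjects, arms not separated | yes |
| Diet | both | active only | active only | given to subjects, arms not separated | yes |
| Withania and multivitamin (placebo in control) | active only | active only | active only | active only | yes |
| Acupressure | not listed | not listed | active only | active only | no |

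The three descriptions that set out both arms' content agree on exercise and counselling: both arms receive them. They disagree on diet. Acupressure separates the arms but is missing from the hypothesis.

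**2. What the between-arm difference estimates**

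Let m0 be the mean BAI with no programme, mS the mean under the shared programme with placebo (control arm), and mSA the mean under the shared programme plus the active-only components (active arm).

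- Effect named in the objective and null: mSA − m0.
- Effect the randomised comparison estimates: mSA − mS.
- Gap between them: (mSA − m0) − (mSA − mS) = mS − m0, the effect of the shared programme.

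No arm supplies m0, so the gap cannot be estimated at any sample size. This does not depend on the component effects being additive.

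**3. How many named components drop out**

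The hypothesis names five: diet, exercise, counselling, Withania and multivitamin. Exercise and counselling are shared in all three arm descriptions, so at least two of five are outside the test. Diet makes it three of five only if the Participants paragraph governs. If the Intervention paragraph and the Methodology govern, diet belongs to the tested add-on.

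**4. Whether another analysis could carry the package claim**

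Only change from baseline within the active arm refers to the whole package. Section 4.0 says that uncontrolled studies are prone to bias and that a control group is needed to interpret change. Within-arm change can be described, but on the Protocol's own reasoning it cannot support a causal claim for the package.

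**5. Whether the sample size settles the matter**

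The inflation step reproduces: 54 / (1 − 0.30) = 77.1, rounded up to 78. The 54 cannot be reproduced, because no standard deviation or baseline BAI is given. The section sizes a parallel-group trial for a 40% difference but describes its two populations as pre- and post-treatment. It therefore does not say whether the 40% is the package effect or the add-on effect. Nothing in this point rests on these figures.

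**The case against.** The best defence is that the contrast is disclosed. The Participants paragraph sets out what control receives shortly after the null, the Methodology repeats what both groups get, and the planned test is plainly between arms. An add-on design is legitimate, and neither randomisation nor the test is harmed. All of that stands. It makes the fault one of a hypothesis that does not match a valid design, not of the design itself. It does not remove the fault, because no part of the Protocol restates the aim as an add-on effect.

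The phrase in section 4.0 about the control group can also be read as not receiving the full active package, which is true. Read that way it is loose. It remains inaccurate for the components that control does receive.

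A reader might infer that section 4.0 rules out any before/after comparison. It does not: it keeps change in the treatment group as an interest and objects to studies without a control.

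It is also fair to say that a non-significant result never proves absence of effect. The problem here goes further: even a precisely estimated between-arm difference of zero would be compatible with a large improvement in both arms.

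Finally, the Methodology says the active group will continue behavioural psychotherapy, which might suggest that counselling later differs between arms. The same section gives it to both groups, so this does not make counselling an active-only component.

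**Conclusion.** The point holds. The objective and null attribute to the whole package an effect that the trial can test only as an increment over exercise encouragement and counselling or cognitive-behavioural treatment. At least two of the five named components fall outside the test. The increment itself is not fixed, because the diet descriptions conflict and the active-only acupressure is absent from the hypothesis.

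This rests on reading the arm descriptions as written and on no numerical assumption. The objective, the null and the account of the control group are fixed in the Protocol, so a separate analysis plan would not make them correct.

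Two stronger readings are not supported. A reader might infer that diet drops out of the comparison as well; that follows from the Participants paragraph alone and is contradicted by the Intervention paragraph and the Methodology. A reader might also infer that the trial will see some known fraction of the planned 40% difference. The Protocol gives no effect for the shared programme and does not say which effect the 40% represents, so no such fraction can be derived.

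**What to change.** 1. Reconcile the descriptions of the two arms in the abstract (Participants and Intervention), the Methodology and section 3.3, so that each component is marked once as shared or active-only. Which description of diet is right is for the sponsor and investigators to settle.
2. Then restate the objective and null. For example: the components given only to the active arm (listed by name, including acupressure, and diet if it proves to be active-only) produce no difference in BAI between the arms when added to the programme that both arms receive.
3. Align section 3.0, Outcome measurements and section 4.0 with that wording, and describe the control group in 4.0 as receiving the shared programme plus placebo.
4. State that no efficacy conclusion will be drawn for components given to both arms.

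The cost is Protocol wording. This point alone requires no change to sample size, visits or randomisation. The price is a narrower conclusion: the trial would report an add-on effect and could not claim that the package as a whole works.

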**Sample size determination**

Assuming a normal distribution with variances between both populations (pre and post treatment) being essentially equal, we made our power size calculations using Jan deLeeuw's Web-Based Statistics: The Study of Stability in Variation[24]. To obtain a power of 80% with a two sided 5% significance level we would need 54 participants to complete this two-treatment parallel-design study. This will enable the detection of a 40% difference in the Beck Anxiety Inventory rating scale, an amount considered to be clinically significant. Assuming a drop out rate of 30% we will need 78 subjects to commence the trial so that 54 will complete the trial.

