## 5.3 Funding and industry involvement

Support for the study has been generously provided by Canada Post Corporation, Canadian Union of Postal Workers, and Swiss Herbals through the Research Department of the Canadian College of Naturopathic Medicine. Funding to the college is under the control of the chief financial officer at The Canadian College of Naturopathic Medicine, see appendix E. Beyond the confines of this trial, none of the investigators, nor the supervising physician involved have any ties or relationships with Swiss Herbals.

This trial was registered with the International Standard Randomized Clinical Trial Registry (trial registration number: ISRCTM78958974 available at <http://www.controlled-trials.com/isrctn/search.html?srch=ISRCTN78958974&sort=3&dir=desc&max=10>). Registration of this trial took place after the trial had been completed due to a number of complications with previous submissions and delays in the registration process. We additionally recognize a lack of knowledge on the part of the authors with regards to clinical trial registration – initially it was our understanding that because the trial was taking place within a workplace setting, registration was not necessary. After recognizing our error and misunderstanding, we proceeded with a registration attempt. We declare that this delay was **in no part** due to conflicts of interest, or an attempt to avoid open knowledge of the existence, conduct or results of the trial.

- 1. **Relevance**

Anxiety disorders are among the most prevalent psychiatric disorders in the Canada Post workers general population. Anxiety disorders are associated with considerable chronicity, morbidity, and disability. The economic costs of anxiety disorders include psychiatric, and nonpsychiatric emergency care; hospitalization; prescription drugs; reduced productivity; absenteeism from work; and suicide. We aim to evaluate the efficacy of typical Naturopathic treatment on anxiety. This will also lay the groundwork for an assessment of the cost effectiveness of Naturopathic Medicine in the treatment of anxiety in the work place.

.

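### The abstract lists three unranked main outcomes, the rest of the protocol rests on the BAI, and no test day is named, so the two-sided 5% is not secured

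*Protocol*

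**What the plan says.** Protocol section 2.0 (Scientific abstract) describes three questionnaires under "Main Outcome Measures", with no ranking and no time point:

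- the BAI, with one total score;
- the SF-36, with eight separately scored domains and two summary scores that can be derived from them;
- the Fatigue Questionnaire, for which no total-score rule is given.

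Elsewhere the protocol is narrower. The objective and null hypothesis in the same abstract concern anxiety scores only. The Outcome measurements section judges the interventions "as measured by the Beck Anxiety Inventory as shown in appendix A" and names no other instrument. Sample size determination states: "To obtain a power of 80% with a two sided 5% significance level we would need 54 participants to complete this two-treatment parallel-design study". It continues: "This will enable the detection of a 40% difference in the Beck Anxiety Inventory rating scale, an amount considered to be clinically significant".

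On timing, the abstract and Methodology have all three instruments completed on treatment at Days 28, 56 and 84. Methodology has both arms complete the BAI and S-90-R together with the "SF-36, Fatigue Questionnaire, and the Perceived Benefit of Treatment questionnaires at 4, 8, and 12 weeks", and mails the package again at 2, 6 and 12 months. The abstract calls Day 84 the final assessment and Methodology calls it the end of treatment. Neither makes it the day of the test.

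The Statistical Analysis paragraph says that data from a menopause scale, which is not an instrument of this trial, will be analysed by chi-square and t-test. It names no endpoint and no day.

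**The concern.** A 5% error rate belongs to a specific comparison: one outcome, at one time, tested once. The protocol sizes the trial on a single BAI comparison, but its abstract offers three instruments as main outcomes, and no section fixes the day. The analysis paragraph, which ought to settle both questions, names a scale from a different condition.

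What is at stake is freedom to choose the headline result after seeing the data. A reader who accepts the BAI as the deciding outcome still cannot tell from the protocol whether a difference at Day 28 or Day 56 would count. A reader of the abstract alone could take an SF-36 domain or the fatigue score as a main result. Choosing an analysis plan's methods can be left to a later document. Which outcome is primary, and when, is what the sample size rests on, and here the protocol addresses it inconsistently.

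**Working it through.** **Inputs from the protocol.** Two-sided 5%, 80% power, 54 completers, 30% drop-out, 78 to start (Sample size determination); three on-treatment assessments at Days 28, 56 and 84 (abstract, Methodology). **Assumptions.** 1:1 allocation, so 27 completers per arm; one fatigue score; the correlations shown below.

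**The plan's own figures.** The drop-out step reproduces: 54/(1 - 0.30) = 77.1, rounded up to 78. The 54 cannot be reproduced, because no SD and no reference BAI mean are given; the text says only "Assuming a normal distribution with variances between both populations (pre and post treatment) being essentially equal". With 27 per arm, the normal approximation implies a standardised difference of (1.960 + 0.842) × √(2/27) = 0.76.

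**Count of main scores.** BAI 1 + SF-36 domains 8 + SF-36 summaries 2 + fatigue 1 = 12.

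**Method.** For k independent tests at 5%, the chance of at least one false positive is 1 - 0.95^k. For correlated tests, k standard normal statistics with common correlation r were simulated (400,000 draws) and the share with any |z| > 1.96 was counted. By Šidák's inequality the independence figure is an upper bound for correlated two-sided normal tests.

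**One BAI comparison on one fixed day (k = 1).** 5%, as stated.

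**BAI at any of three visits (k = 3).**
- Independent: 1 - 0.95^3 = 14.3%
- r = 0.3: 13.6%
- r = 0.5: 12.6%
- r = 0.7: 10.9%

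**Any of 12 scores at one visit (k = 12).**
- Independent: 1 - 0.95^12 = 46.0%
- r = 0.3: 39.7%
- r = 0.5: 31.8%
- r = 0.7: 23.1%
- r = 0.9: 13.4%

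**Cost of keeping all 12 as main outcomes.** Bonferroni gives 0.05/12 = 0.00417 per test, with critical value 2.865. At the implied effect size, power with 27 per arm is Φ(0.762 × √(27/2) - 2.865) = Φ(2.802 - 2.865), about 47%. Restoring 80% would take 96 completers, and 96/0.70 = 137.1, so 138 to start.

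**The case against.** The strongest reply is that the protocol points to the BAI nearly everywhere that matters: the null hypothesis, the outcome section, the sample size and the entry score. The abstract describes the BAI first and nowhere states that the three instruments are co-primary or that success on any one is enough. The SF-36 summaries are presented as scores that can be obtained, not as planned tests. Section 4.0 justifies 84 days as long enough to show a clinically significant effect, which together with the abstract and Methodology points to Day 84. Multiplicity rules for further outcomes may sit in an analysis plan that is not at hand.

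Much of this stands, and it limits the claim in three ways.

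- A reader might infer that the stated 5% is false. The documents do not support that: it is stated only for the BAI comparison and is correct for it once one day is fixed.
- A reader might take the 12-score figures as the trial's error rate. They need a rule that any listed score counts, which no section states. The 46% also assumes independence, which cannot hold when the SF-36 summaries are built from its own domains.
- Section 5.3 says "Registration of this trial took place after the trial had been completed". A reader might infer that nothing outside the protocol fixed the outcome in advance. Late registration does not show what an analysis plan or the ethics and regulatory submissions contain.

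What the reply does not remove is the disagreement between the abstract and the other sections, the absence of a named test day, and an analysis paragraph that names the wrong scale.

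**Conclusion.** The protocol contradicts itself on its main outcome and does not name the day of the test, so the two-sided 5% is not secured by the text. On the reading the protocol favours, with the BAI as the deciding outcome, the exposure is the open choice among three on-treatment visits: about 11-14%, for an assumed between-visit correlation of 0.7 down to 0.3. On the wider reading, where any of the 12 listed scores at one visit could count, it is about 13-40% for an assumed common correlation of 0.9 down to 0.3, with 46% as the ceiling. That second range is conditional on a rule the protocol does not contain. The count of 12 rests on treating fatigue as one score. The defect is in core protocol content, and it goes away once one outcome and one day are named.

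**What to change.** In the abstract, Outcome measurements, Sample size determination and Statistical Analysis, name one primary outcome: the between-arm difference in BAI total at Day 84, tested at two-sided 5%. In Statistical Analysis, replace the menopause scale with the BAI and say which of the two named tests applies to this comparison. Label the SF-36, the Fatigue Questionnaire, the SCL-90-R (written S-90-R in Methodology) and the BAI at Day 28, Day 56 and follow-up as secondary, reported with confidence intervals and with no efficacy claim resting on them alone. Section 3.3 should also list the BAI at Day 84: its entry for that day omits it, while the Schedule of events includes it.

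The cost is wording only. This point leaves the 54 completers and 78 starters unchanged. The downside is that a positive SF-36 or fatigue result can no longer be the trial's headline.
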